### Safety evaluation

Every patient enrolled in the trial will be assessed for the occurrence of adverse events (AEs). The incidence rate of AEs will be measured as the main safety outcome. The following measures will be used to evaluate the safety of the study drug:
Breath rate per minute, pulse rate per minute, heartbeat rate per minute, diastolic and systolic blood pressure, and sitting position (mmHg)Electrocardiogram (ECG) and the number of patients with an abnormal 12-lead ECG reportAssessment of the Columbia-Suicide Severity Rating ScaleAssessment of the Arizona Sexual Experience ScaleNumber of patients with AEs resulting in early withdrawalNumber of patients with serious adverse events (SAEs) resulting in early withdrawalNumber of emerging AEs during the drug withdrawal period

### Sample size determination

The sample size estimation was based on the results for an analysis of covariance (ANCOVA) comparing changes in the MADRS score from baseline to the last assessment in the 8-week treatment of the study drug or placebo. Reference was made to the results from the phase IIb trial in which the decrease in the MADRS total score in the study drug group was 16.04 and 12.75 in the placebo group. Using a significance level of 5%, a power of 80%, a SD of 8.5, and a dropout rate of 20%, the sample size was estimated to be 133 per group.

### Statistical analysis

Full analysis set for clinical effectiveness analysis and compliance evaluation, and safety analysis set for safety evaluation will be performed in the study. The statistical analysis software will be SAS version 9.4 or above. All statistical tests will be double-sided, and *P*-values less than or equal to 0.05 will be considered statistically significant. The statistical analysis shall be carried out according to the statistical analysis plan. Descriptive statistics for cases will be the percentages (%); descriptive statistics for measurement data will describe the number of cases, mean, standard deviation, median, minimum, and maximum. Change score outcomes will be adjusted for baseline values to prevent regression to the mean.

### Primary efficacy analysis

The treatment effect will be evaluated using ANCOVA with the study drug group, site, depressive episode, and baseline MADRS total score as the explanatory variables. The 95% confidence intervals and *P*-values will be presented. Missing data will be handled using the multiple imputation approach.

### Secondary efficacy analysis

Clinical remission rate as assessed using MADRS and HAMD-17 at the end of the study will be analyzed using ordinal logistic regression as the (proportional) odds ratio of Anyu Peibo versus placebo with a two-sided Wald 95% confidence interval. Treatment, baseline MADRS (total score under beyond or under 30) or HAMD-17 (higher or lower than the median), site, and depressive episode (single episode or relapse) will be included in the model.

The *t*-tests with a two-sided alpha level of 0.05 will be used to analyze the following variables: total MADRS scores, MADRS scores over time, CGI-I scores at different visits, and the changes in total scores from baseline for the HAMD-17, HAMA, CGI-S, DSST, TMT A and B, and SDS. The mean differences in the scores and the 95% confidence intervals for Anyu Peibo compared to placebo will be used as the estimate of the treatment effect.

The estimate of the difference in the proportions of patients withdrawing due to poor efficacy and the proportions of patients using combined medication to treat insomnia (Anyu Peibo versus placebo), 95% confidence intervals, and chi-square *P*-values will be calculated. In the cases of low cell frequencies (< 5), the Fisher exact test will be used instead.

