### Participants and eligibility

Patients diagnosed with MDD at the time of screening will be enrolled across 14 sites in China. The trial period will be from July 2019 to December 2020. The inclusion, exclusion, and withdrawal criteria in AYPB-MDD-III (Table 1) have been chosen to exclude patients at risk of suicide.

**Table 1 Tab1:** Inclusion criteria, exclusion criteria, and withdrawal criteria

Inclusion criteria	Exclusion criteria	Withdraw criteria

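### Read plainly, the remission model estimates about 13 site coefficients at 19 patients per site, which slightly overstates a real treatment odds ratio; conditioning on site removes most of the excess at almost no cost

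*Protocol article*

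**What the plan says.** The Secondary outcomes section of the protocol article defines remission as a MADRS total of at most 10 and a HAMD-17 total of at most 7 at the end of the study. Both endpoints are binary. The Secondary efficacy analysis section assigns them an ordinal (proportional-odds) logistic regression, reported as an odds ratio "with a two-sided Wald 95% confidence interval". With two outcome categories this is ordinary binary logistic regression. The covariates are treatment, a two-level baseline score, "site, and depressive episode (single episode or relapse) will be included in the model". No random site effect, conditioning, penalty or pooling of sites is mentioned.

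Patients "will be enrolled across 14 sites in China", and "the sample size was estimated to be 133 per group". The article gives neither expected site sizes nor expected remission rates. The Statistical analysis section refers the analysis to a separate statistical analysis plan, which is not shown.

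**The concern.** The primary ANCOVA also adjusts for site, and there the number of site terms does no harm: in a linear model, extra indicators cost a few degrees of freedom and do not bias the treatment effect. Logistic regression behaves differently. When many intercepts are each estimated from few patients, the unconditional maximum likelihood estimate of a common log odds ratio is biased away from zero. If the drug works, the reported remission odds ratio is somewhat too favourable.

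A second, lesser nuisance is that a site in which every patient or no patient remits has no finite intercept estimate, so the software issues a convergence or separation warning. The stakes are the size of two secondary odds ratios and a clean, pre-specified fit.

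**Working it through.** **Inputs from the protocol article.** 14 sites; 133 per group; 1:1 allocation; MADRS decreases of 16.04 and 12.75; SD 8.5; two-sided 5% level; 80% power; 20% dropout.

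**The plan's own figure.** The difference is 16.04 − 12.75 = 3.29. Then n = 2 × (1.960 + 0.842)² × 8.5² / 3.29² = 104.8, so 105 per group by the normal approximation and 106 by the t distribution. Allowing for dropout, 106 / 0.8 = 132.5, so 133. The stated size is reproduced.

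**Patients per site.** 2 × 133 / 14 = 19.0; with 20% lost, 0.8 × 266 / 14 = 15.2. Site as a categorical covariate uses 14 − 1 = 13 coefficients, besides treatment, baseline and episode.

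**Plausible remission rates (assumption).** Take the change as normal with the figures above and assume a baseline MADRS of 28 to 32. Remission then needs a fall of 18 to 22.
- Placebo: Φ((12.75 − 18)/8.5) = 27% down to Φ((12.75 − 22)/8.5) = 14%.
- Drug: Φ((16.04 − 18)/8.5) = 41% down to Φ((16.04 − 22)/8.5) = 24%.
- Total remissions: about 133 × (0.14 + 0.24) = 51 to 133 × (0.27 + 0.41) = 90.

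Placebo remission of 20-30% is therefore a reasonable working range, though not one the article states.

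**Size of the bias.** Simulated trials of 266 patients in 14 sites, site SD 0.5 on the logit scale, 1,500 runs per setting where the number is recorded. The rows with true OR 2 have no covariates beyond treatment and site; the 30% row with true OR 1.80 adds two.

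| Placebo remission, site sizes | Truth | Site indicators, ordinary ML | Conditional on site | Firth penalised |
|---|---|---|---|---|
| 30%, equal and unequal | log OR 0.588 (OR 1.80) | 0.63-0.64 | 0.60 | 0.59 |
| 20%, equal | log OR 0.588 | 0.626 | 0.592 | not run |
| 20%, equal | OR 2 | 2.10 | 2.02 | 2.00 |
| 20%, 5 to 50 | OR 2 | 2.10 | 2.02 | 2.00 |
| 30%, equal | OR 2 | 2.08 | 2.00 | 1.99 |
| 30%, 5 to 50 | OR 2 | 2.11 | 2.02 | 2.02 |

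- Relative excess: 0.626/0.588 = 1.06, and the 30% setting gives 7-8%. On the odds ratio scale, exp(0.626) = 1.87 and exp(0.64) = 1.90.
- Against the sampling error: (0.626 − 0.588)/0.339 = 0.11, where 0.339 is the root mean squared error of that fit. In the 30% setting the Monte Carlo SE of 0.008 over 1,500 runs implies a per-trial SE of 0.008 × √1500 = 0.31, and 0.08 × 0.588/0.31 = 0.15.
- Fewer analysed patients raise it: with 15 per site (210 in total) and 20-30% placebo remission, the excess in the log odds ratio was 9-11%.
- Not all of it comes from site. With no site heterogeneity and a true OR of 2, the model without site gave 2.03 and with site 2.11, so site adds about 4% to the odds ratio.
- At the null there is no bias. Across all scenarios run (placebo remission 10-30%), type I error was 5.0-6.0% and Wald coverage 93.4-95.4%.

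**Comparison with conditioning on site** (20%, equal sites, true log OR 0.588). Root mean squared error is 0.318 against 0.339, and coverage 95.7% against 94.8%.

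**Sites with all or no remitters.** With 19 patients and a 20% rate in everyone, the chance of no remitter is 0.8¹⁹ = 0.0144 per site. Over 14 identical sites it is 1 − (1 − 0.0144)¹⁴ = 18%. With site SD 0.5 and odds ratios of 1 to 2, simulation gave 14-36% at 20% placebo remission and 3-9% at 30% for equal sites. For sites of 5 to 50 it gave 59-80% and 32-48%.

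Such a site's likelihood contribution is the product of (1 − pᵢ) over its patients, or of pᵢ if all remit. It tends to 1 as that site's intercept goes to minus (or plus) infinity, whatever the treatment coefficient. The treatment estimate is therefore the one obtained with the site left out. In the scenario simulations that tracked it, the treatment log odds ratio was finite in every trial.

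**The case against.** The strongest objection is that the article says only that site enters the model. Fixed indicators fitted by unconditional maximum likelihood are an inference, and the handling of small sites is commonly left to the statistical analysis plan. That stands as a condition on this point: if that plan already conditions on site, or does something equivalent, nothing need change. It does not remove the point, because the article names the model, the interval and the covariates, and the plain reading of those has a cheap and better alternative.

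The bias is also small, partly unrelated to site, and absent at the null. That stands in full.

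A reader might infer more, and the documents do not support it:
- *That an all-or-none site leaves the planned analysis without a result, so sites must be dropped or merged after the outcome is seen.* Only that site's intercept diverges. The treatment odds ratio is finite, and nothing has to be merged. A conditional fit ignores the same sites.
- *That the test is materially anti-conservative.* In one comparison, null rejection was 5.1-5.9% for site indicators and 4.6-5.5% for the conditional fit. With 1,500 runs, each rate has a Monte Carlo SE of √(0.05 × 0.95/1500) = 0.56 percentage points, so these ranges do not establish a meaningful difference.
- *That the key secondary results are compromised.* Remission comes first in the list, but the article does not rank its secondary endpoints.

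**Conclusion.** The point holds as a minor one. With site entered as ordinary indicators at about 19 patients each, the remission log odds ratio is overstated by roughly 6-8% when there is an effect: 1.80 becomes about 1.87-1.90, or about 0.1-0.15 standard errors. Type I error and coverage remain near nominal. Separation at a small site is a matter of warnings, not of a lost treatment estimate.

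The size rests on assumptions that the article does not supply: 20-30% placebo remission, a site SD of 0.5, all 266 patients analysed, and site handled as fixed effects. The primary ANCOVA is not affected.

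**What to change.** For the two binary remission endpoints, replace the site-indicator model with binary logistic regression conditional on site (in SAS, STRATA site in PROC LOGISTIC), keeping treatment, baseline category and episode as covariates. If the statistical analysis plan already specifies an equivalent treatment of site, state that instead. Firth penalisation also removed most of the excess and would be acceptable. Dropping site is not a substitute: when sites differ, it moves the odds ratio towards 1 (at a true OR of 2, 20% remission and site SD 1.0, about 1.83-1.86).

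The cost is one program statement and one sentence of text. The target odds ratio is unchanged, and the reported one will be slightly smaller. Conditioning yields no site intercepts, but the article asks only for the odds ratio and its interval. In return, most of the excess goes, the root mean squared error falls slightly, and the separation warning from all-or-none sites is avoided.

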### Trial management, monitoring, and auditing

An independent DSMB is monitoring the quality of the trial and has access to trial outcomes and accumulated safety data, including adherence, SAEs, suspected unexpected serious adverse reactions, and mortality. In addition, the DSMB will review the safety data from a clinical and safety point of view on an ongoing basis.

The sponsor will perform monitoring visits as frequently as necessary. Representatives from the sponsor’s quality assurance department can visit the trial site at any time during the study to conduct an audit of the study in compliance with the regulatory guidance.

## Discussion

Antidepressants are the first-line recommended treatment for MDD, which is a serious psychological disorder with a high disease burden in adults [27, 28]. However, concerns over the long-term balance of benefits and harms arising from the currently marketed antidepressants point to the need for new antidepressants with improved efficacy and safety.

*Piper laetispicum* C. DC. has been used in Chinese traditional medicine as a sedative and analgesic and to treat toothache and snake bites [29]. The n-hexane extracts from *Laetispicum* C. DC. have been tested for their anti-inflammatory activity against cyclooxygenase-1 and 5-lipoxygenase, showing evidence that extracts of these species act as in vitro inhibitors of both enzymes [30–32]. *Piper* alkamides have been reported to possess various properties, including antidepressant effects. Its anxiolytic and antidepressant effects have been explained by its capability to inhibit monoamine oxidase activity and increase the levels of serotonin and noradrenaline in some regions of the mouse brain [33, 34].

Anyu Peibo Capsule includes the extracted *Piper* alkamides (amide alkaloids), and the administration of Anyu Peibo Capsule has been estimated to improve the MDD clinical outcome with a favorable safety profile in phase IIa and IIb trials. This phase III trial aims to demonstrate a beneficial effect of Anyu Peibo Capsule on patients with MDD, while minimizing the side effects, in particular those relating to sexual dysfunction and gastrointestinal discomfort.

### Limitation

The long-term outcomes of Anyu Peibo were not included in this trial. A substantially larger effect will be demonstrated in a superiority trial.

### Trial status

The trial is currently recruiting and enrolling patients according to version 1.2 of the protocol (August 2019). Recruitment began on January 23, 2020, and the approximate date for completion of recruitment will be in December 2020.

## Data Availability

Not applicable.
